# Effectiveness, Mediators, and Effect Predictors of Internet Interventions for Chronic Cancer-Related Fatigue: The Design and an Analysis Plan of a 3-Armed Randomized Controlled Trial

**DOI:** 10.2196/resprot.4363

**Published:** 2015-06-23

**Keywords:** fatigue, cancer survivors, chronic disease, Internet interventions, mindfulness-based cognitive therapy, motor activity, behavior therapy, accelerometry, effect predictors, mediation, Bayesian statistics, latent growth analysis

## Abstract

**Background:**

Internet interventions offer advantages that especially cancer survivors who suffer from fatigue could benefit from. Given the growing number of such patients, Internet interventions could supplement and strengthen currently available health care.

**Objective:**

This paper describes the design and analysis plan that will be used to study 2 Internet interventions aimed at reducing severe fatigue in cancer survivors: a mobile ambulant activity feedback therapy supported through a weekly email by a physiotherapist and a weekly Web- and mindfulness-based cognitive therapy supported online by a psychologist. The data resulting from this trial will be used to (1) investigate the effectiveness, (2) investigate potential mediators of these interventions, and (3) explore participant characteristics that can predict the effect of these interventions.

**Methods:**

A 3-armed randomized controlled trial is proposed that compares both Internet interventions with an active control condition that solely consists of receiving psycho-educational emails. The intervention period is 9 weeks for all 3 conditions. Six months after baseline, participants in the control condition can choose to follow 1 of the 2 experimental Internet interventions. Outcomes are measured in terms of fatigue severity, mental health, and self-perceived work ability. All are Web-assessed at baseline, 2 weeks after the intervention period, and at 6 and 12 months after baseline. Fatigue severity, mindfulness, physical activity, expectations and credibility of the intervention, therapeutic working alliance, sleep quality, and sense of control over fatigue are assessed 3 times during the intervention period for identifying mediators of the interventions. Recruitment is performed nationally throughout the Netherlands through patient organizations and their websites, newspapers, and by informing various types of health professionals. All participants register at an open-access website. We aim at including 330 cancer survivors who have finished curative-intent cancer treatment at least 3 months previously, and have been suffering from severe fatigue ever since. All cancer types are included. A detailed analysis plan is described to address the research questions, which allows for individual variation, and fully exploits the longitudinal design.

**Results:**

Recruitment started in April 2013 and will proceed until April 2015.

**Conclusions:**

This paper describes a systematic trial design for studying 2 different interventions for chronic cancer-related fatigue in order to gain insight into the effectiveness and mediators of the interventions. This design will also be used to identify predictors for the interventions’ effect on fatigue. By publishing our hypotheses and analysis plan before completion of data collection, this paper is a first step in reporting on this trial comprehensively.

**Trial Registration:**

The Netherlands National Trial Register (NTR3483). (Archived by WebCite at http://www.webcitation.org/6NWZqon3o).

## Introduction

### Background

Behavioral interventions have shown to effectively relieve psychological and physical complaints in cancer survivors. However, the effect on the individual is less explicit, because patients differ greatly in the ways they experience and respond to such interventions. Therefore, when studying such an intervention, individual differences and temporal aspects need to be appreciated. This paper presents a detailed analysis plan for studying behavioral interventions that satisfies such needs.

The protocol of a 3-armed randomized controlled trial is described to study the effectiveness, mediators, and effect predictors of 2 different Internet interventions that share the same aim: reducing fatigue for cancer survivors. Due to its longitudinal design and multiple assessments during the intervention, the temporal development of relevant factors rather than pre-post differences can be studied. Latent growth analysis can be performed and mixture models can be run, which allow for individual variance in growth trajectories. Furthermore, full longitudinal mediation analyses can be performed on the most important potential mediators of both interventions, and differentiating effect predictors can be identified in order to allocate individuals to the most suitable intervention.

The goal of this paper is to present our trial design, hypotheses, and analysis plan. This paper will therefore be the basis for a number of papers that will present the results of the trial. We will first provide brief background information on the research population, the relevance of Internet interventions for this population, and introduce the 2 Internet interventions that are the subject of this trial. Next, the importance of identifying mediating and predicting factors for the intervention effect is discussed. In the remaining sections, we give a detailed description of the trial’s design, our hypotheses, and the analysis plan for handling the data that the trial will collect. The analysis plan is written in general terms, in order to facilitate the use of this strategy in other contexts, and to keep this paper focused. Consequently, the extended background of—and reasoning for—the specific hypotheses will be presented in future papers that will focus on the results of the proposed analyses.

### Chronic Fatigue and Cancer

Cancer-related fatigue is defined as “a persistent, subjective sense of physical, emotional and/or cognitive tiredness or exhaustion related to cancer or cancer treatment that is not proportional to recent activity, and interferes with usual functioning” [1]. It is 1 of the most prevalent and distressing long-term consequences of cancer [2], interferes with the activities of daily living, work ability [3], and maintenance of social relations, and consequently impacts patients’ well-being [4]. As the number of cancer survivors in the Netherlands is expected to increase rapidly, with a growth of over 50% in the 10-year prevalence between 2009 and 2020 [5], there is a strong need for effective and accessible treatments.

The etiology of cancer-related fatigue probably involves the deregulation of several interrelated physiological, biochemical, and psychological systems [6]. There is no definite somatic explanation for the persistence of fatigue after cancer [7-9], and estimates of the proportion of cancer survivors who suffer from persistent fatigue vary widely [8,10]. However, research has shown that if fatigue continues 3 months after treatment, it is unlikely to decrease of its own accord [8]. The term chronic cancer-related fatigue (CCRF) is used in this paper for severe fatigue that continues for 3 months or longer after cancer treatment completion.

### Management of Chronic Cancer-Related Fatigue

Currently, both pharmacological treatments and nonpharmacological treatments are applied to the effective management of CCRF; see the overview articles published by Ahlberg et al [9] and Koornstra et al [11]. Guidelines state that if no primary association can be found for the persistence of fatigue with a somatic condition, behavioral interventions should also be considered [1]. The previously reported effects of nonpharmacological interventions on fatigue vary widely, as can be seen in the overview of recent meta-analyses in Table 1. Effect sizes tend to be higher when the intervention targets fatigue, and when increased fatigue was an inclusion criterion for the study. Not all studies that were included in the meta-analyses primarily targeted fatigue, therefore effect sizes might not be representative for nonpharmacological interventions that target fatigue.

**Table 1 table1:** Ten recent meta-analyses considering nonpharmacological interventions for cancer patients that included off-treatment fatigue.

Meta-analyses (off treatment)	Intervention type	ES^a^ (95% CI)	Fatigue reduced (*P*-value)
Jacobsen 2007 (k^b^=4%)	Psychological	d^c^ = 0.10 (0.02-0.18)	Yes (<.05) [12]
Jacobsen 2007 (k=29%)	Activity-based	d=0.05 (-0.08-0.19)	ns [12]
Kangas 2008 (100%)	Psychological	WMES^d^(r^e^) = 0.51 (0.10-0.92)	Yes (.015) [13]
Kangas 2008 (100%)	Exercise	WMES(r) = 0.13 (-0.77-1.02)	ns (.784) [13]
Speck 2010 (100%)	Exercise	WMES(r) = 0.54 (0.19-0.90)	Yes (.003) [14]
Brown 2011 (k=54%)	Exercise	WMES(r) = 0.31 (0.22-0.40)	Yes [15]
Duijts 2011 (n=31%)	Behavioral techniques	SMD^f^(f^g^) = 0.16 (0.08-0.23)	Yes (<.001) [16]
Duijts 2011 (n^h^=42%)	Exercise	SMD(r) = 0.315 (0.10-0.53)	Yes (.004) [16]
Cramp 2012 (100%)	Exercise	SMD = 0.37 (0.18-0.55)	Yes [17]
Tomlinson 2014 (100%)	Exercise	SMD(r) = 0.61 (0.33-0.88)	Yes [18]

^a^ES = Effect size; values are positive when the intervention was able to reduce fatigue more compared to the control condition.

^b^k=percentage of studies

^c^d=Cohen’s d

^d^WMES = weighted means effect size

^e^r=random effects

^f^SMD = standardized mean difference

^g^f=fixed effects

^h^n=percentage of participants

Behavioral interventions are often based on energy balance models and/or stress coping models [12,19]. In energy balance models, CCRF is seen as a consequence of deconditioning and prolonged inactivity during cancer and its treatment. Secondary fatigue arises as a result of detraining and can lead to a downward spiral. In stress coping models, CCRF is conceptualized as a result of ineffective coping strategies and prolonged stress response [20]. Cognitive behavioral treatments that are based on these theories include physical activity interventions, exercise interventions [14,17,21,15,22], and mindfulness-based cognitive interventions [23-26] and have been shown to help reduce CCRF in previous studies [12,13]. However, all these interventions require the patient to travel to a health care facility, which can be a burden to the patient. Therefore, introducing effective interventions in a home-based setting could improve the health care options for this group.

### Potential Benefits of Internet Interventions

Internet interventions offer advantages that cancer survivors who suffer from fatigue could especially benefit from. They have been found to be as effective as face-to-face therapies for a wide range of disorders, such as posttraumatic stress disorder, burnout or chronic stress, and depression [27-32]. Internet interventions have the ability to reach a wider range of patients compared to face-to-face interventions, especially severely fatigued patients, those with limited mobility, or patients in rural or even remote areas. Also, patients may benefit from the home-based setting of Internet interventions as these patients can practice more often, are less bound to the availability of care professionals, and can incorporate the intended behavioral change directly into their daily routine. Moreover, visiting a health care facility may no longer be desirable for some cancer survivors due to negative associations with the disease process or because they no longer want to be identified as a cancer patient and prefer the anonymity of their own environment.

### Internet Interventions for Fatigue

#### Overview

In the Netherlands, to our best knowledge there are currently 3 Internet interventions that aim to reduce chronic fatigue: (1) an experimental mobile intervention aimed at changing physical activity behavior for participants with chronic fatigue syndrome [33]; (2) the Web-based mindfulness-based cognitive therapy “Minder Moe Bij Kanker” [34]; and (3) a Web-based cognitive behavior therapy for severely fatigued breast cancer survivors, which is the subject of the current CHANGE study (trial registration NTR4309) [35].

This paper describes the design and analysis plan that studies the first 2 of these Internet interventions in a randomized controlled trial. Each of these 2 interventions is described below.

#### Mobile Activity Management Intervention: Ambulant Activity Feedback Therapy

The ambulant activity feedback therapy (AAF) is a mobile intervention that utilizes an ambulant activity coaching system, supported weekly by a physiotherapist through email [33]. The activity coaching system was developed by Roessingh Research and Development (Enschede, The Netherlands) and consists of a mobile phone and an accelerometer (Multimedia Appendix 1) that communicate through Bluetooth [33].

In this intervention, the patient works to meet personal activity goals and subgoals that will be defined together with the therapist. The coaching system supports this process by showing real-time feedback about the accumulated activity of the patient relative to a personalized line of reference and tailored hourly feedback messages. Both the line of reference and the set of feedback messages of the activity coaching system can be adjusted by the therapist through a Web portal (see Figure 1 and Multimedia Appendix 2). Patients also have access to a Web portal where they can monitor their past personal activity records. Consequently, patients are expected to gain insight in their activity pattern and on how to increase or balance their daily activity in a way that improves their energy levels. More information about AAF is given in [name] and [name] (in press) [36].

**Figure 1 figure1:**
[figure not shown]
Screenshot of the Web portal for the ambulant activity feedback therapy (Dutch).

#### Web-Based Mindfulness-Based Cognitive Therapy

Mindfulness-based cognitive therapy (MBCT) [37] adds elements of cognitive therapy to the mindfulness-based stress reduction program that was originally developed by John Kabat-Zinn [38]. The Helen Dowling Institute (Bilthoven, the Netherlands) developed a 9-week Web-based, therapist-guided, individual MBCT (eMBCT) specifically designed to reduce cancer-related fatigue [23]. On a personal Web page (see Figure 2 and Multimedia Appendix 3), each patient can download audio files of mindfulness exercises and read information about a specific mindfulness theme each week. Patients write down their experiences of following the mindfulness exercises in a log. On an agreed-upon day of the week, the therapist replies to this log, thereby guiding the patient through the program. It is hypothesized that by learning to raise awareness of their present experience nonjudgmentally and openly, the patient can become aware of potentially ineffective coping strategies that prolong stress and fatigue [39,40]. Patients learn to use a detached perspective as a skill to prevent the escalation of automatic negative thinking patterns. MBCT also teaches patients how to accept fatigue, physical limitations, or pain. The protocol of the eMBCT is discussed more extensively in the article by [name] et al [34].

**Figure 2 figure2:**
[figure not shown]
Screenshot of the Web portal for eMBCT (Dutch).

### Effectiveness

#### Overview

Our primary question is whether both interventions are effective in reducing fatigue. Therefore, the interventions will be compared to an active control group in a randomized controlled trial. The advantage of this design, as compared to a waiting-list control group, is that we can control for nonspecific influences of the trial, such as receiving attention. Also, we expect that in an active control group, fewer participants will drop out than in a waiting-list control group.

Usually, results of interventions are presented in terms of an average improvement of the relevant outcome measure. However, practice shows that individuals benefit differently from interventions [41]. Therefore, the proposed trial will aim to identify individual fatigue trajectories, since that seems to be more informative and helpful in improving health care provisions for CCRF-patients than just presenting averages.

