## Methods

### Design

A randomized controlled trial is performed including 3 parallel conditions: 2 experimental conditions (AAF and eMBCT) and a minimal intervention control condition. The intervention period is 9 weeks for all 3 conditions. Both experimental conditions are made as similar as possible in terms of time-investment and contact intensity with the therapist. Outcomes are self-reported and are Web-assessed at baseline (T0), 2 weeks post-intervention (T1), and at 6 months (T2) and 12 months (T3) after baseline. Figure 3 shows a schematic summary of the trial design.

The baseline assessment consists of 3 time-points: (1) T0a, the assessment to check eligibility; (2) T0b, the main baseline assessment taken after the eligibility check and informed consent, but naive of condition; and (3) T0c, directly after randomization for assessing the participant’s credibility and expectancy about the condition. All participants are invited to fill out short questionnaires in weeks 1, 2, 3, 4, 6, and 9 (Mi) of the intervention period in order to study mediation of the interventions.

After T2, patients in the control condition are offered 1 of the 2 experimental interventions, again in a research setting. Please note that the first 4 participants of this trial were randomized to 1 of the experimental conditions for the second semester, but to minimize dropout, all other patients will be allocated based on their own preference. During this second intervention period, these participants will again be assessed in weeks 1, 2, 3, 4, 6, and 9 (Mi’), the second week after the intervention (T1’), and 6 months after the second allocation (T2’). Participants in the control condition that are preferentially allocated to eMBCT after T2 do not wear the accelerometer during the second semester.

The protocol allows delay within the intervention period of a maximum of 2 weeks in case of, for example, illness or holiday. For all participants, the duration of their participation is approximately 12 months. Additional qualitative feedback will be obtained through explorative interviews with a subset of participants in the experimental condition shortly after T1 or T1’.

This trial was approved by the Twente Medical Ethical Committee (Enschede, the Netherlands) under number P12-26 and has been registered at The Netherlands National Trial Register under number NTR3483 [42].

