#### Randomization

If the eligibility-criteria are met, the researcher confirms the participant’s enrollment. Subsequently, the activity sensor is given to the participant and its setup is explained in a face-to-face meeting in the participant’s home or another mutually convenient location. The second baseline assessment starts (T0b), followed by randomization of the participant to 1 of the 3 conditions by a script embedded in the researchers’ Web portal and uses the random function of php (rand(1,3)) [50]. The researchers can neither influence nor predict the outcome of the randomization process. Subsequently, the researcher emails the participant about the outcome of randomization, requests the participant to complete the third baseline assessment (T0c), and assigns the participant to a therapist in case the participant has been randomized to an experimental condition. Participants who do not fill out T0c are considered as not being included. The allocation of a therapist is based on current availability of the therapists who are involved in the trial.

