#### Active Control Condition

Patients who are assigned to the control condition receive weekly emails containing standard psycho-educational texts about CCRF in order to minimize the dropout rate, following the design of Postel et al [51]. An example of the information that is offered in this minimal intervention control condition is given in Multimedia Appendix 4 and overlaps completely with the information that is given during both experimental interventions. This condition controls for receiving information on CCRF and for being involved in eHealth research.

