**Figure 5 figure5:**
[figure not shown]
Simplified representation of a correlated growth model in which Iy and Sy represent the intercept and slope factors of the latent growth model of the outcome parameter, and Iz and Sz represent the latent growth factors of the mediator. H1-4 represent the 4 subhypotheses of Step 6. All indicators have been left out for clarity.

###### Step 7

The next step in studying potential working mechanisms is a single-step, multiple-mediation analysis using structural equation modeling [104-106]. By estimating such a model, we expect to obtain a comprehensive model for all the working mechanisms of the intervention. It should be noted that this model assumes that an intervention works in the same way for all participants in a particular group [107]. Again, data from both semesters will be used.

A separate model will be tested for each intervention. Each model will have the following paths (Figure 6), where X=independent variable (1/0 for specific intervention vs control group), Y=outcome variable (difference score T2-T0b of the primary outcome measure), and Z=mediator:

a: X regressed on Z.b: Z regressed on Y;c’: direct effect of X on Y.

For each experimental intervention, the starting model will consist of all the significant primary mediators of Step 6 that have also been assessed in the control group. In other words, the factors that have shown to be mediators in the correlated growth model will be the starting point for this model. The models will then be complemented with the secondary mediating factors described in Textbox 2. Mediating factors for which the indirect effect (a × b) is insignificant will be removed stepwise, after which a final model will be created.

Model fit, standardized path coefficients—including indirect effects—and the total effect of at least the first and final models will be reported with 95% confidence intervals.

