## Discussion

### Principal Findings

This paper has described the design, hypotheses and analysis plan of a randomized controlled trial in order to study the effectiveness, mediation, and effect predictors of 2 Internet-based interventions for CCRF. Although recruitment and inclusion have already started, publishing the analysis plan is of great value because it will help to prevent outcome reporting bias [110] and adds validity information to the final studies [111].

By using multiple assessments during the intervention, the proposed trial design is suitable for studying the chronological development of both potential mediators and fatigue. That has 2 main advantages. Firstly, the data will be suitable for analyses that allow for variation in the individual fatigue trajectories. We do not expect that either of the interventions that have been included in the trial will be beneficial for all participants: our study sample will be highly heterogeneous considering for example tumor and treatment types. Therefore, the analyses on individual growth trajectories can acknowledge that expectation and test that hypothesis. This will substantiate the interpretation of the results on effectiveness and will be an important first step in identifying what works for whom. Secondly, this study design enables us to use a fully longitudinal mediation analysis, at least for the most important factors, rather than using indirect effects analysis in cross-sectional mediation analysis.

Another important feature of the proposed design is that by comparing 2 different interventions with an active control group, therapy-specific elements of the interventions can be distillated from the data acquired during this trial. This advantage counts for both the effect predictors and the mediators. Knowledge about such differentiating factors can and should be used to better inform patients with CCRF and to improve allocation of patients with CCRF to suitable interventions. As a result, an increase in the overall effectiveness of relevant interventions can be established.

In this paper, we have presented the trial design, our hypotheses, and a detailed analysis plan. In accordance with good clinical practice, and to avoid outcome reporting bias, this paper was submitted before any of the data was analyzed. All methods are now openly predetermined, therefore any future publication describing this trial can be valued reliably on its quality.

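### The control arm is credited with controlling for attention, but it has no therapist and deferred access, so the primary contrast is guided package versus information emails

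*Protocol article*

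**What the plan says.** The Introduction (Effectiveness, Overview) explains why a waiting list was not used: with an active control, "we can control for nonspecific influences of the trial, such as receiving attention". The Discussion (Principal Findings) builds on this: "by comparing 2 different interventions with an active control group, therapy-specific elements of the interventions can be distillated from the data".

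The arm itself is described more modestly. The Abstract calls it "an active control condition that solely consists of receiving psycho-educational emails". Under Active Control Condition, participants "receive weekly emails containing standard psycho-educational texts about CCRF in order to minimize the dropout rate", and the section ends: "This condition controls for receiving information on CCRF and for being involved in eHealth research". Under Randomization, the researcher "assigns the participant to a therapist in case the participant has been randomized to an experimental condition". Under Design, contact is matched between the two active arms only: "Both experimental conditions are made as similar as possible in terms of time-investment and contact intensity with the therapist". The same section says controls are offered one of the two interventions after T2 (6 months).

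Step 7 of the analysis plan starts its mediation model from "all the significant primary mediators of Step 6 that have also been assessed in the control group" and expects a full account of how each intervention works.

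**The concern.** The property claimed in the Introduction is not one that the described arm has. The two active arms differ from control in content, in individual therapist contact, and in whether the participant is still awaiting an intervention at 6 months. All three differences coincide with allocation.

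What is at stake is how a positive result may be read. Lower 6-month fatigue than control would support the whole guided package over information emails. It would not show that mindfulness content or activity feedback did more than weekly contact with a therapist would have done. A reader relying on the Introduction or the Discussion could take it to show that.

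**Working it through.** The point rests on the comparator, so the check sets the sections side by side.

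1. **Claimed scope.** The Introduction says nonspecific influences, attention included. Active Control Condition says information on fatigue and taking part in eHealth research. Attention is absent from the second list, and the stated purpose of the emails there is to limit dropout.

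2. **Therapist contact.** AAF has weekly support from a physiotherapist by email. In eMBCT a therapist answers the patient's log on a fixed day each week. Controls are assigned no therapist. Over the 9-week period this is weekly individual contact against none, in both intervention-versus-control comparisons.

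3. **Access to treatment.** The between-group hypotheses in Textbox 1 are set at 6 months. Controls are offered an intervention after that assessment, so they are awaiting access throughout the primary comparison.

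4. **Sensitivity of the outcome.** Design says outcomes are self-reported, and Step 1 says participants are not blinded. Contact and waiting can therefore plausibly move the score.

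5. **Can the planned models separate these?** Contact and waiting status are fixed by allocation, so an intervention-versus-control contrast gives one difference and cannot divide it. More participants would narrow its interval without changing this.

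6. **Step 7.** Working alliance is a primary mediator in Table 2 and a hypothesised generic mediator in Textbox 2. An arm without a therapist has no alliance to rate (an inference; Table 2 does not mark assessments by arm). Step 7's entry rule then leaves alliance out. Any effect through alliance stays in the direct path c' or is picked up by correlated mediators, so the model cannot cover all working mechanisms.

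7. **The contact-matched comparison.** AAF versus eMBCT is the only pair matched on time and contact. Every between-group effectiveness hypothesis in Textbox 1 is against control, and no effectiveness step tests AAF against eMBCT, although the Step 1 model already estimates separate slopes for all three arms.

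8. **Precision of that contrast.** Assume a plain difference of two means in SD units, without baseline adjustment: half-width = 1.96 × √(1/n₁ + 1/n₂).
   - Planned, 77 per experimental arm at T2: 1.96 × √(1/77 + 1/77) = 1.96 × 0.161 = 0.32 SD.
   - Planned, 77 against 94 controls: 1.96 × √(1/77 + 1/94) = 1.96 × 0.154 = 0.30 SD.
   - At the January 2015 group sizes, 36 AAF and 24 eMBCT: 1.96 × √(1/36 + 1/24) = 1.96 × 0.264 = 0.52 SD. These are interim counts, with recruitment still open and no allowance for attrition.

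   At the planned size the contrast is nearly as precise as the primary ones. It is imprecise for its purpose because two active arms are likely to differ by less than either differs from control.

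**The case against.** The strongest reply is that the Introduction's sentence is comparative. It speaks of influences of the trial, relative to a waiting list, and on that reading it has support. Everyone has a face-to-face sensor meeting before randomisation, everyone is invited to questionnaires in six of the intervention weeks, and controls hear from the study weekly with information that both interventions also give. Design openly calls the arm a minimal intervention. This stands for research participation and minimal attention. It does not extend to individual attention from a therapist.

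Nor does the plan rest specificity on the control arm alone. Subhypothesis 4 of Step 6 requires a specific mediator's slope to exceed those in the other groups, which include the other experimental arm, and Step 8 compares effect predictors across all three groups. This stands, with the caveat that Step 6 also uses second-semester data from participants who chose their intervention, so that comparison is not wholly randomised.

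The added contrast does not cure the confounding either. AAF and eMBCT share therapist contact, so their difference says nothing about how much of a shared benefit is due to contact. That is correct and limits what the contrast is for.

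Three stronger readings are tempting and unsupported. A reader might infer that the authors will report a positive result as an effect beyond attention; no section says so, and the primary question is only whether the interventions reduce fatigue. A reader might infer that controls were promised treatment and were disappointed; the text says it is offered and may be chosen, and does not say when participants are told. A reader might also want to put a share on attention; nothing in the documents identifies one.

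**Conclusion.** The concern holds in a limited form. The Introduction claims more for the control arm than its own description supports, and the Discussion's statement about therapy-specific elements needs a qualification. Each randomised comparison remains valid as therapist-guided package versus information emails with deferred access, and no planned estimate or test is invalidated. What fails is attributing a difference from control to treatment content.

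The issue affects both primary comparisons, and contact and deferral overlap completely with allocation. Its numerical contribution is unknown and cannot be recovered from those comparisons. The conclusion assumes that controls have no therapist contact during the first 6 months, as the text implies, and that contact or waiting could affect self-reported fatigue. It should be corrected, because it changes what a positive result may be said to show.

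**What to change.** 1. In the Introduction, limit the claim to what Active Control Condition supports: information and research participation. In Principal Findings, add that therapy-specific statements do not rest on intervention-versus-control differences. Word effectiveness conclusions as therapist-guided package versus information-only emails with deferred access.

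2. From the Step 1 model, report the AAF-versus-eMBCT difference in 6-month fatigue with its 95% CI, labelled as a secondary contrast. State that it will be imprecise, that it can show only differential content, and that it cannot show how much of a shared benefit is due to attention.

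3. In Step 7, state that c' includes therapist contact and alliance, and drop the expectation that the model covers every mechanism. Keep specificity claims on the Step 6 subhypothesis 4 comparison, which includes the other experimental arm.

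The cost is a few sentences and one contrast from a model already planned. The price is a narrower claim and a secondary estimate that may well be inconclusive.
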